***Control arm of the trial.***

Participants in the control arm will receive a letter from the researcher telling them they are in the control arm; they will receive generic health information material e.g. on smoking cessation, increasing physical activity. Participants in the control arm will be asked to complete an on-line questionnaire at three months. (In order to maximise follow up rates participants who don’t complete the on-line questionnaire will be offered a telephone alternative.) They will be informed that we will contact them towards the end of the trial period, to identify anyone who may wish to be interviewed. At the end of the trial period they will meet again with the researcher and complete the profiler. They will receive a copy of their LIBRA score and profile and will be given access to the In-MINDD on-line support environment.

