At three months, participants will be asked to complete an on-line questionnaire about risk factor(s) they have selected and the steps and actions they have taken, if any, to reduce that or those risk factors. This questionnaire will address risk factors they selected, what they have learned about reducing that risk factor, what steps/actions they took to follow the advice given, how they have accessed those activities and how often and whether they are still participating in those activities. They will also be asked if they would be willing to be interviewed about their experience so far in In-MINDD. In addition, use of the In-MINDD support environment will be monitored remotely, e.g. how often they access the systems; for how long; and what sites they visit.

After six months participants will meet with the researcher or practice nurse again and update their information on the In-MINDD system in order to generate a final LIBRA score and profile.

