**Summary schedule of assessments**

| **In-MINDD arm of trial** | **Control arm of trial** |
| --- | --- |
| IN-MINDD baseline data collection meeting with researcher  (Eligibility checked, consent obtained, baseline data collected) – 1 hour | IN-MINDD baseline data collection meeting with researcher  (Eligibility checked, consent obtained, baseline data collected) – 1 hour |
| Participants receive letter informing which arm of the trial they are allocated to. | Participants receive letter informing which arm of the trial they are allocated to. |
| Participants access In-MINDD online support site and views LIBRA score. | Participants receive printed generic health information |
| Participants attend GP practice to discuss profiler result and personalised plan. |  |
| During this six month period participants are invited to access In-MINDD support environment and set goals for health related behaviour change. |  |
| At three months participants are asked to complete an online questionnaire | At three months participants are asked to complete an online questionnaire |
| After six months participants meet with researcher or practice nurse to update information and receive a final LIBRA score | After six months participants meet with researcher or practice nurse to update information and receive a final LIBRA score |

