***11b. Discontinuing or modifying the intervention.***

Participants will be able to leave the trial, if they wish to, at any time and for any reason. An end of trial form will be completed for all trial members, detailing the reason for leaving the trial e.g. choosing to leave; illness; death; loss to follow-up.

As this is a feasibility trial, we are particularly interested in monitoring the sustainability of use of the In-MINDD intervention. This is not a medical or pharmaceutical intervention, so we will not modify the delivery of the intervention but, instead, monitor how participants use and adapt the system to suit their own needs. In particular, we are interested in exploring the actions taken by those in the In-MINDD arm in comparison with those in the control arm. For example, will the information about modifiable risk factors for dementia given to participants in the control arm prompt them to modify their lifestyle behaviour of their own volition (e.g. will simply knowing that smoking increases the risk of developing dementia encourage them to seek out information about smoking cessation and attempt to reduce their smoking or stop smoking completely; will knowing that obesity and physical inactivity increases the risk of developing dementia encourage them to take action to increase physical activity).

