**Three month follow-up**

Complete online questionnaire

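### The telephone fallback for the three-month online questionnaire is written only under the control arm, so response and mode of collection may differ between arms in the exploratory comparison of actions taken

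*Protocol*

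**What the plan says.** Section 11a of the protocol describes the three-month follow-up separately for each arm.

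- **In-MINDD arm of trial:** "At three months, participants will be asked to complete an on-line questionnaire about risk factor(s) they have selected" and about the steps they have taken. No other way of completing it is mentioned.
- **Control arm of the trial:** "Participants in the control arm will be asked to complete an on-line questionnaire at three months". A bracketed sentence follows. It opens "In order to maximise follow up rates participants who" and goes on to say that those who do not "complete the on-line questionnaire will be offered a telephone alternative".
- **Summary schedule of assessments:** both columns carry the same entry, "At three months participants are asked to complete an online questionnaire".
- **CONSORT diagram (Participant timeline):** both three-month boxes show an online questionnaire only, for example "Complete online questionnaire".

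On use of the data, section 11b says "we are interested in exploring the actions taken by those in the In-MINDD arm in comparison with those in the control arm". Section 11c says that questionnaires at three and six months will assess which behaviours participants targeted and how far they kept them up.

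**The concern.** A follow-up procedure in a randomised comparison should be the same in each arm. Here an extra route to a completed questionnaire is written for one arm and not for the other. If four national teams work from this text, some or all may telephone control non-responders and leave In-MINDD non-responders missing.

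Two things could then differ by arm for reasons unrelated to any effect of the intervention. The first is who is in the sample: the control responders would include people who ignored the online form, and the In-MINDD responders would not. People who ignore an online form in the In-MINDD arm may well include those who stopped using the online system, so their answers bear on sustainability of use, which section 11c treats as a key question. The second is mode: some control answers would be given by telephone, while all In-MINDD answers would be given online.

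Answers that were never collected cannot be recovered by a later analysis plan, so this belongs in the protocol's data-collection rules.

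**Working it through.** **Step 1: is the fallback given to the In-MINDD arm anywhere?** The three-month questionnaire appears in the two arm descriptions in section 11a, the schedule, the two CONSORT boxes and section 11c. The telephone option appears once, in the control-arm description. Section 11c has a rule that is not arm-specific for people with whom contact is lost, but it only has the team ask the practice whether the patient is still registered. It is not another way to complete the questionnaire. No section extends the fallback to the In-MINDD arm, and none excludes that arm.

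**Step 2: how does the sentence read in place?** It says participants, without qualification. The sentence before it names the control arm, and the sentence after it (about contact near the end of the trial) also concerns controls. Read in sequence it applies to controls, but the wording does not settle this.

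**Step 3: what could follow if it is applied to controls only?** The protocol gives no expected response rate, so every rate below is an assumption. Let

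- q = online response, equal in both arms
- f = share of control non-responders recovered by telephone
- p1 = proportion of online responders reporting an action
- p0 = the same proportion among non-responders

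There is no true difference between arms and, for now, no mode effect.

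Response gap (control minus In-MINDD) = (1 − q)f

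Share of control answers given by telephone: w = (1 − q)f / [q + (1 − q)f]

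Spurious difference (In-MINDD minus control) = p1 − [q·p1 + (1 − q)f·p0] / [q + (1 − q)f] = w(p1 − p0)

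*One case in counts.* 600 participants randomised equally give 300 per arm. With q = 0.6, 180 respond online in each arm. With f = 0.5, the telephone recovers 60 of 120 control non-responders, so control response is 240/300 = 80% against 60%. With p1 = 0.6 and p0 = 0.3, controls show (108 + 18)/240 = 52.5% against 108/180 = 60%, a spurious 7.5 points.

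*Range for q = 0.5 to 0.8 and f = 0.25 to 0.75.* The response gap runs from 0.2 × 0.25 = 5 points to 0.5 × 0.75 = 37.5 points. The weight w runs from 0.05/0.85 = 0.059 to 0.375/0.875 = 0.429.

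| p1 / p0 (assumed) | Spurious difference, percentage points |
|---|---|
| 0.50 / 0.50 | 0 |
| 0.55 / 0.45 | 0.6 to 4.3 |
| 0.60 / 0.40 | 1.2 to 8.6 |
| 0.60 / 0.30 | 1.8 to 12.9 |

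The result is driven by p1 − p0, about which the protocol says nothing.

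**Step 4: is the direction fixed?** No. If being asked by telephone shifts the reported proportion by m, the difference becomes w(p1 − p0 − m). A positive m equal to p1 − p0 cancels it, a larger m reverses it in favour of control, and a negative m enlarges it. Equal online response is also an assumption. If it were 70% in the In-MINDD arm and 60% in controls, f = 0.25 would bring controls to 0.6 + 0.4 × 0.25 = 70% and close the response gap.

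**Step 5: which outcomes does it reach?** The Outcomes section names the global risk score as primary and changes in individual risk factors as secondary. The score comes from the profiler, completed at baseline and again at six months. The three-month questionnaire is not the source of either outcome.

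**The case against.** The strongest reply is that this is a misplaced sentence and not a design decision. The aside speaks of participants in general and gives a purpose, better follow-up, that applies equally to both arms. The schedule and the diagram also treat the arms alike at three months. That is a fair reading, and it rules out claiming that the protocol deliberately denies the fallback to the In-MINDD arm. It does not remove the need to act: if a common rule was meant, it is in the wrong place and is missing everywhere else a team would look.

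A second reply is that little depends on these data. Section 11b speaks only of exploring, does not tie the comparison to this questionnaire alone, and six-month questionnaires and interviews also inform it. As described for the In-MINDD arm, the questionnaire asks about selected risk factors and following advice, and the protocol does not establish a common item on which both arms would be compared. This stands. It limits the point to an exploratory comparison and means that the percentages above illustrate a mechanism and are not a forecast for a defined endpoint.

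A reader might also infer that the extra contact would raise control-arm retention at six months and so touch the primary outcome. Nothing in the protocol supports that. Both arms are followed up in person at six months, and the In-MINDD arm has its own contacts: a practice or telephone consultation and email reminders.

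**Conclusion.** The point holds in a limited form. The telephone fallback is written for the control arm only and is absent from the In-MINDD text, the schedule and the CONSORT diagram. Applied as written, response and mode of collection may differ by arm, and this may bias the exploratory comparison of actions taken. The primary and secondary outcomes are not shown to be affected.

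It is tempting to conclude that the comparison will be biased and that In-MINDD will look better. The protocol does not support that. The range of 0 to about 13 points rests on assumed response, recovery and behaviour rates, with equal online response in both arms and no mode effect. The difference is 0 if non-responders act like responders, and its sign can change once mode or unequal online response is allowed for. This is a cheap improvement, not a threat to the trial's main result.

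**What to change.** Take the sentence out of the control-arm text and state one rule for both arms: anyone who has not completed the three-month questionnaire by the same fixed time is offered the same telephone version, with the same script. Bring the two arm descriptions in section 11a, the summary schedule of assessments and both three-month CONSORT boxes into line with it. Record the mode of completion for each questionnaire, and report response and mode by arm.

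With equal response and recovery rates and equal behaviour across arms, a common rule brings both the response gap and the selection difference in the illustration to 0. Recording mode lets any remaining imbalance be seen. The cost is a few sentences of protocol wording, one recorded field, and telephone calls to In-MINDD non-responders. The sample size and the defined outcomes do not change.

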***Process evaluation.***

A process evaluation, focussed on patients, will be conducted in each partner country. Additional work, interviewing more patients and practitioners, will be conducted in Scotland and Ireland.

As participants approach the end of the trial period, we will contact them and ask if they would be willing to participate in a face-to-face interview. At the end of the trial a sample of participants will be selected from those agreeing to be approached for interview or focus group. A minimum of 12 patients will be interviewed in each country; interviewees will be selected on the basis of LIBRA score (high and low); gender (male and female). Interviews will be conducted at a time and place convenient to the interviewee and will last approximately 1 hour. This work will to explore their views of the information they received from the profiler, their use of the on-line support environment, and how they did/did not incorporate recommendations into their daily life. A discussion of their perception of the overall benefit of the In-MINDD experience will also take place.

A larger process evaluation will be conducted in Scotland, where interviews will be conducted with 20 to 25 participants. A smaller group of participants in the control group (n=10) will also be interviewed in order to ascertain whether the information they received increased their understanding of the modifiable risk factors for dementia and whether they made any lifestyle changes. Efforts will also be made to obtain an understanding of why participants did not complete the trial by including a sample of those who dropped out.

We also intend to explore health professionals’ expectations and opinion about reducing dementia risk and the In-MINDD system. We will do this through both semi-structured interviews and focus groups. We will ask a minimum of three health professionals (GPS, practice nurses and other appropriate staff members) from each of the six participating practices to contribute to this work which will take place at the beginning of the trial and again at the end of the trial. Staff will be interviewed about their views of dementia; the use of risk scores and how such information is shared with patients; preventive strategies for dementia; and the In-MINDD profiler.

Written consent will be obtained from both patients and professionals prior to interview or focus group. Interviews and focus groups will be recorded and transcribed verbatim. Data analysis will use recognised methods of qualitative analysis ^13^, underpinned by Normalisation Process Theory ^6,8^. Analyses will be conducted both within country and by sharing anonymised transcripts between countries via video conferenced data coding clinics.

**Summary schedule of assessments**

| **In-MINDD arm of trial** | **Control arm of trial** |
| --- | --- |
| IN-MINDD baseline data collection meeting with researcher  (Eligibility checked, consent obtained, baseline data collected) – 1 hour | IN-MINDD baseline data collection meeting with researcher  (Eligibility checked, consent obtained, baseline data collected) – 1 hour |
| Participants receive letter informing which arm of the trial they are allocated to. | Participants receive letter informing which arm of the trial they are allocated to. |
| Participants access In-MINDD online support site and views LIBRA score. | Participants receive printed generic health information |
| Participants attend GP practice to discuss profiler result and personalised plan. |  |
| During this six month period participants are invited to access In-MINDD support environment and set goals for health related behaviour change. |  |
| At three months participants are asked to complete an online questionnaire | At three months participants are asked to complete an online questionnaire |
| After six months participants meet with researcher or practice nurse to update information and receive a final LIBRA score | After six months participants meet with researcher or practice nurse to update information and receive a final LIBRA score |

***11b. Discontinuing or modifying the intervention.***

Participants will be able to leave the trial, if they wish to, at any time and for any reason. An end of trial form will be completed for all trial members, detailing the reason for leaving the trial e.g. choosing to leave; illness; death; loss to follow-up.

As this is a feasibility trial, we are particularly interested in monitoring the sustainability of use of the In-MINDD intervention. This is not a medical or pharmaceutical intervention, so we will not modify the delivery of the intervention but, instead, monitor how participants use and adapt the system to suit their own needs. In particular, we are interested in exploring the actions taken by those in the In-MINDD arm in comparison with those in the control arm. For example, will the information about modifiable risk factors for dementia given to participants in the control arm prompt them to modify their lifestyle behaviour of their own volition (e.g. will simply knowing that smoking increases the risk of developing dementia encourage them to seek out information about smoking cessation and attempt to reduce their smoking or stop smoking completely; will knowing that obesity and physical inactivity increases the risk of developing dementia encourage them to take action to increase physical activity).

***11c. Improving adherence.***

We will monitor use of the In-MINDD on-line support environment remotely, e.g. how often they access the systems; for how long; and what sites they visit. Questionnaires at 3 and 6 months will assess what areas of lifestyle behavioural change participants targeted e.g. smoking cessation; taking up a new hobby such as learning a language, and to what extent they have maintained that activity. Participants will be recruited through general practices; if contact is lost at either 3 or 6 months, we will be able to contact the practice to ascertain if the patient is still registered with the practice or if they have left. This will be documented by the local country team. We will not, however, remove patients from the trial is they do not use the In-MINDD on-line environment, as likelihood and sustainability of use are key research questions.

***11d. Concomitant care.***

We will not actively prohibit other care interventions during the trial, but will ask about activities that may support or mitigate against In-MINDD. We will also interview participants randomised to the In-MINDD intervention arm; in Scotland, we will also interview control arm patients.

1. ***Outcomes***

Primary outcome: global risk score, calculated on the basis of a basket of individual risk factors identified from work package 1 of In-MINDD. These will include physical and cognitive activity; mood; presence of diabetes, chronic kidney disease and/or cardiovascular disease; high cholesterol; unhealthy diet; smoking status; alcohol consumption; hypertension; and obesity.

Secondary outcomes: changes in individual risk factors.

1. **Participant timeline**

**CONSORT Diagram.**

**Assessment of eligibility.**

Conducted in the practice based on age; medical stability and presence of one or more IN-MINDD risk factors which are readily available to practices e.g. age band and smoker; age band, diabetic and smoker.

Practice or research team to invite patient to participate.

**Control arm**

**IN-MINDD arm**

**Randomisation.**

Stratified by country and (possibly) by practice; researcher writes to participant

**2 Weeks**

Researcher adds in additional clinical information from practice; generates dementia risk score.

**Excluded.**

Don’t meet initial inclusion criteria; Declined to participate; Other reason

**Recruitment and baseline meeting.**

Verification of eligibility by researcher; Informed consent.

Baseline data collection, by completion of IN-MINDD profiler.

**Excluded.**

Don’t meet initial inclusion criteria; Declined to participate; Other reason

**1 month**

Visit practice or telephone consultation to obtain LIBRA score & profile; discussion

Interviews with sample of participants, between 3 and 6 months

**Six month follow-up**

Meet researcher; complete profiler; receive old and new LIBRA score & profile

**Six month follow-up**

Meet researcher; complete profiler; receive new LIBRA score & profile

**Three month follow-up**

Complete online questionnaire

**Three month follow-up**

Complete on-line questionnaire

**Control arm**

**IN-MINDD arm**

1. **Sample size**

Power calculations - Sample size = 600, power (.8) to detect a small effect size (.187 or.2) - indicate that 150 patients per partner country, randomised into either the In-MINDD group or a control group, will be sufficient to confidently show evidence of effect over the timescale of the randomised controlled trial.

1. **Recruitment**

Practice records will be screened on the basis of the inclusion criteria described in Section 10. Screening will be undertaken by either the research team or practice staff in Ireland, The Netherlands and France or by a recognised proxy in Scotland (Scottish Primary Care Research Network). Once eligible patients have been identified, GPs will screen the list to ensure that only suitable participants are approached. The researcher or practice, as appropriate, will then write to eligible patients to ask if they are interested in participating in IN-MINDD. (In Scotland, letters will be sent from participating practices with support of SPCRN).

Patients will be sent an information pack about In-MINDD, including participant information sheets and an expression of interest form, which is returned to the research team. Patients expressing an interest will be contacted by the research team and invited to meet with he researcher; at that meeting eligibility will be confirmed and consent to participate in the study will be obtained. We will assume a response rate of 10 - 20% (based on recent experience of recruitment for similar studies) for our initial mailing and we will repeat mailings until our sample size has been achieved.

1. **Allocation**

***16a. Sequence generation***

The Robertson Centre for Biostatistics, University of Glasgow will carry out the process of randomisation. Randomisation will be stratified by country and practice to ensure an even balance of participants across both arms of the trial, both within practices and between partner countries. The allocation will be derived using a computer generated randomisation schedule.

